### **Expedited Reporting of Adverse Events**

For the purpose of regulatory reporting, Celgene Corporation Drug Safety will determine the expectedness of events suspected of being related to lenalidomide based on the Investigator Brochure.

For countries within the European Economic Area (EEA), Celgene Corporation will report in an expedited manner to Regulatory Authorities and Ethics Committees concerned, SUSARs in accordance with Directive 2001/20/EC and the Detailed Guidance on collection, verification and presentation of adverse reaction reports arising from clinical trials on medicinal products for human use (ENTR/CT3) and also in accordance with country-specific requirements.

For the purpose of regulatory reporting in the EEA, Celgene Corporation Drug Safety will determine the expectedness of events suspected of being related to the other investigational medicinal product (IMP), cetuximab, based on the SmPC for this product.

Celgene Corporation shall notify the Investigator of the following information:

Any AE associated with the use of investigational product(s) in this study or in other studies that is both serious and unexpected, i.e., suspected unexpected serious adverse reaction (SUSAR)

Any finding from tests in laboratory animals that suggests a significant risk for human subjects including reports of mutagenicity, teratogenicity, or carcinogenicity.

Where required by local legislation, the Investigator shall notify his/her IRB/IEC promptly of these new serious and unexpected AE(s) or significant risks to subjects.

The Investigator must keep copies of all pertinent safety information, including correspondence with Celgene Corporation and the IRB/IEC, on file (see Section 18.3 for records retention information).

### **21.3. Lenalidomide Pregnancy Risk Minimisation Plan for Celgene Clinical Trials (Ex-EU territories)**

Section 21.3 applies to all patients receiving lenalidomide therapy. The following Pregnancy Risk Minimisation Plan documents are included in this section:

1. Lenalidomide Risks of Fetal Exposure, Pregnancy Testing Guidelines and Acceptable Birth Control Methods (Section 21.3.1);
  2. Lenalidomide Education and Counselling Guidance Document (Section 21.3.2);
  3. Lenalidomide Patient Card (Section 21.3.3) and,
  4. Lenalidomide Information Sheet (Section 21.3.4).
1. The Lenalidomide Risks of Fetal Exposure, Pregnancy Testing Guidelines and Acceptable Birth Control Methods document (Section 21.3.1) provides the following information:
    - Risks to the foetus associated with lenalidomide exposure
    - Definition of Woman of Childbearing Potential
    - Pregnancy testing requirements for patients receiving Lenalidomide who are women of childbearing potential
    - Acceptable birth control methods for both woman of childbearing potential and male patients receiving Lenalidomide in the study
    - Requirements for counselling of all study patients receiving Lenalidomide about pregnancy precautions and the potential risks of foetal exposure to lenalidomide
  2. The Lenalidomide Education and Counselling Guidance Document (Section 21.3.2) must be completed and signed by either a trained counsellor or the Investigator at the participating clinical centre prior to each dispensing of lenalidomide study treatment. A copy of this document must be maintained in the patient records.
  3. The Lenalidomide Patient Card (Section 21.3.3) will be completed by the Investigator for each patient receiving lenalidomide study therapy prior to the start of lenalidomide study treatment. For women of childbearing potential, all study-related pregnancy tests will be recorded on this patient card.

The Lenalidomide Information Sheet (Section 21.3.4) will be given to each patient receiving lenalidomide study therapy. The patient must read this document prior to starting lenalidomide study treatment.

### **21.3.1. Lenalidomide Risks of Fetal Exposure, Pregnancy Testing Guidelines and Acceptable Birth Control Methods**

#### **Risks Associated with Pregnancy**

Lenalidomide is structurally related to thalidomide. Thalidomide is a known human teratogenic active substance that causes severe life-threatening birth defects. An embryofoetal development study in animals indicates that lenalidomide produced malformations in the offspring of female monkeys who received the drug during pregnancy. The teratogenic effect of lenalidomide in humans cannot be ruled out. Therefore, a risk minimization plan to prevent pregnancy must be observed.

#### Criteria for woman of childbearing potential (WCBP)

This protocol defines a woman of childbearing potential as a sexually mature woman who: 1) has not undergone a hysterectomy or bilateral oophorectomy or 2) has not been naturally postmenopausal (amenorrhea following cancer therapy does not rule out childbearing potential) for at least 24 consecutive months (i.e., has had menses at any time in the preceding 24 consecutive months).

#### Counselling

For a woman of childbearing potential, lenalidomide is contraindicated unless all of the following are met (i.e., all women of childbearing potential must be counselled concerning the following risks and requirements prior to the start of lenalidomide study therapy):

- She understands the potential teratogenic risk to the unborn child
- She understands the need for effective contraception, without interruption, 4 weeks before starting study treatment, throughout the entire duration of study treatment, dose interruption and 28 days after the end of study treatment
- She should be capable of complying with effective contraceptive measures
- She is informed and understands the potential consequences of pregnancy and the need to notify her study doctor immediately if there is a risk of pregnancy
- She understands the need to commence the study treatment as soon as lenalidomide is dispensed following a negative pregnancy test
- She understands the need and accepts to undergo pregnancy testing based on the frequency outlined in this protocol ([Table 2](#)).
- She acknowledges that she understands the hazards and necessary precautions associated with the use of lenalidomide

The investigator must ensure that for women of childbearing potential:

- Complies with the conditions for pregnancy risk minimization, including confirmation that she has an adequate level of understanding
- Acknowledge the aforementioned requirements

For a woman NOT of childbearing potential, lenalidomide is contraindicated unless all of the following are met (i.e., all women NOT of childbearing potential must be counselled concerning the following risks and requirements prior to the start of lenalidomide study therapy):

- She acknowledges that she understands the hazards and necessary precautions associated with the use of lenalidomide

Traces of lenalidomide have been found in semen. Male patients taking lenalidomide must meet the following conditions (i.e., all males must be counselled concerning the following risks and requirements prior to the start of lenalidomide study therapy):

- Understand the potential teratogenic risk if engaged in sexual activity with a woman of childbearing potential
- Understand the need for the use of a condom even if he has had a vasectomy, if engaged in sexual activity with a woman of childbearing potential.

### Contraception

Women of childbearing potential (WCBP) enrolled in this protocol must agree to use two reliable forms of contraception simultaneously or to practice complete abstinence from heterosexual intercourse during the following time periods related to this study: 1) for at least 28 days before starting investigational product; 2) while participating in the study; 3) dose interruptions; and 4) for at least 28 days after study treatment discontinuation.

The two methods of reliable contraception must include one highly effective method and one additional effective (barrier) method. WCBP must be referred to a qualified provider of contraceptive methods if needed. The following are examples of highly effective and additional effective methods of contraception:

- Highly effective methods:
  - Intrauterine device (IUD)
  - Hormonal (birth control pills, injections, implants)
  - Tubal ligation
  - Partner's vasectomy
- Additional effective methods:
  - Male condom
  - Diaphragm
  - Cervical Cap

Implants and levonorgestrel-releasing intrauterine systems are associated with an increased risk of infection at the time of insertion and irregular vaginal bleeding. Prophylactic antibiotics should be considered particularly in patients with neutropenia.

### Pregnancy testing

Medically supervised pregnancy tests with a minimum sensitivity of 25 mIU/mL must be performed for women of childbearing potential, including women of childbearing potential who commit to complete abstinence, as outlined below.

**Before starting investigational product**

*Female Patients:*

WCBP must have two negative pregnancy tests (sensitivity of at least 25 mIU/mL) prior to starting lenalidomide. The first pregnancy test must be performed within 10-14 days prior to the start of lenalidomide and the second pregnancy test must be performed within 24 hours prior to the start of lenalidomide. The patient may not receive investigational product until the Investigator has verified that the results of these pregnancy tests are negative.

*Male Patients:*

Must practice complete abstinence or agree to use a condom during sexual contact with women of childbearing potential while participating in the study, during dose interruptions and for at least 28 days following investigational product discontinuation, even if he has undergone a successful vasectomy.

**During study participation and for 28 days following investigational product discontinuation**

*Female Patients:*

- WCBP with regular or no menstrual cycles must agree to have pregnancy tests weekly for the first 28 days of study participation and then every 28 days while on study, at study discontinuation, and at day 28 following investigational product discontinuation. If menstrual cycles are irregular, the pregnancy testing must occur weekly for the first 28 days and then every 14 days while on study, at study discontinuation, and at days 14 and 28 following investigational product discontinuation.
- At each visit, the Investigator must confirm with the WCBP that she is continuing to use two reliable methods of birth control at each visit.
- Counselling about pregnancy precautions and the potential risks of foetal exposure must be conducted at a minimum of every 28 days.
- If pregnancy or a positive pregnancy test does occur in a study patient, lenalidomide must be immediately discontinued.
- Pregnancy testing and counselling must be performed if a patient misses her period or if her pregnancy test or her menstrual bleeding is abnormal. Investigational product treatment must be discontinued during this evaluation.
- Women must agree to abstain from breastfeeding during study participation and for at least 28 days after investigational product discontinuation.

*Male Patients:*

- Counselling about the requirement for condom use during sexual contact with women of childbearing potential and the potential risks of foetal exposure must be conducted at a minimum of every 28 days.
- If pregnancy or a positive pregnancy test does occur in the partner of a male study patient during study participation, the investigator must be notified immediately.

Additional precautions

- Patients should be instructed never to give this medicinal product to another person and to return any unused capsules to the Investigator at the end of treatment.
- Female patients should not donate blood during therapy and for at least 28 days following discontinuation of lenalidomide.
- Male patients should not donate blood, semen or sperm during therapy or for at least 28 days following discontinuation of lenalidomide.

Only enough lenalidomide for one cycle of therapy may be dispensed with each cycle of therapy.

### 21.3.2. Lenalidomide Education and Counselling Guidance Document

Protocol Number: \_\_\_\_\_

Patient Name (Print): \_\_\_\_\_ DOB: \_\_\_\_/\_\_\_\_/\_\_\_\_ (mm/dd/yyyy)

Female:

If female, check one:

- ☐ WCBP (Woman of childbearing potential): sexually mature female who: 1) has not undergone a hysterectomy (the surgical removal of the uterus) or bilateral oophorectomy (the surgical removal of both ovaries) or 2) has not been naturally postmenopausal (amenorrhea following cancer therapy does not rule out childbearing potential) for at least 24 consecutive months (i.e., has had menses at any time during the preceding 24 consecutive months)
- ☐ NOT WCBP

Male:

**To be completed prior to each dispensing of lenalidomide.**

#### **Do Not Dispense lenalidomide if:**

- The patient is pregnant.
- No pregnancy tests were conducted for a WCBP.
- The patient states she/he did not use TWO reliable methods of birth control (unless practicing complete abstinence of heterosexual intercourse) [at least 28 days prior, during, dose interruption and 28 days after discontinuation of lenalidomide].

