#### **9.1.3. Pregnancy**

7. Women of childbearing potential must undergo pregnancy testing based on the frequency outlined in Section 21.3 or 21.4 and pregnancy results must be negative.
8. Unless practicing complete abstinence from heterosexual intercourse, sexually active WCBP must agree to use adequate contraceptive methods as specified in Section 21.3 or 21.4.
9. Males (including those who have had a vasectomy) must use barrier contraception (condom) when engaging in sexual activity with WCBP as specified in Section 21.3 or 21.4.
10. Males must agree not to donate semen or sperm during the duration specified in Section 21.3 or 21.4.
11. All subjects must:
  - Understand that the investigational product could have a potential teratogenic risk.
  - Agree to abstain from donating blood while taking investigational product and following discontinuation of investigational product (see Section 21.3 or 21.4).
  - Agree not to share study medication with another person.
  - Be counseled about pregnancy precautions and risks of fetal exposure (see Section 21.3 or 21.4).

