### **10.3. Dose Modification or Interruption**

Dose modifications of lenalidomide and cetuximab are not permitted during Cycle 1 of the Phase 2a – Safety Lead-In part, unless a subject experiences a DLT, however permitted anytime after Cycle 1 during Phase 2a – Safety Lead-In, anytime during Phase 2b –POC and Phase 2b – Expansion.

For toxicities consistent with cetuximab administration, discontinuation, dose interruptions and/or reductions see Section 10.3.2 and the approved product labeling. If toxicities are believed to be attributed to lenalidomide administration, please see Table 6 for dose modification guidelines. Doses of any investigational product cannot be re-escalated once reduced. Any investigational product (lenalidomide and/or cetuximab) held > 14 days must be discontinued. If cetuximab is discontinued per protocol and for reasons other than disease progression, lenalidomide may be continued until documented tumor progression, unacceptable toxicity, death, or treatment discontinuation for any other reason.

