**MALE:**

1. I counselled the Male patient regarding the following:
  - Potential foetal harm (Refer to item #2 in WCBP).
  - To engage in complete abstinence or use a condom when engaging in sexual intercourse (including those who have had a vasectomy) with a woman of childbearing potential, while taking lenalidomide, during dose interruptions and for 28 days after stopping lenalidomide.
  - Males should notify their study doctor when their female partner becomes pregnant and female partners of males taking lenalidomide should be advised to call their healthcare provider immediately if they get pregnant
  - NEVER share lenalidomide with anyone else.
  - Do not donate blood, semen or sperm while taking lenalidomide and for 28 days after stopping lenalidomide.
  - Do not break, chew, or open lenalidomide capsules.
  - Return unused lenalidomide capsules to the investigator.
2. Provide Lenalidomide Information Sheet to the patient.

Investigator/Counsellor Name (Print): \_\_\_\_\_  
(circle applicable)

Investigator/Counsellor Signature: \_\_\_\_\_  
\_\_\_\_\_/\_\_\_\_\_/\_\_\_\_\_

Date:

(circle applicable)

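### The ex-EU pre-dispensing form applies a two-method contraception rule to non-abstinent men, contradicting the condom-only rule in criterion 9, Section 21.3.1 and the form's own male section

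*Protocol*

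**What the plan says.** **The form's status.** Section 21.3, the pregnancy plan for territories outside the EU, says of the Section 21.3.2 form that it "must be completed and signed by either a trained counsellor or the Investigator at the participating clinical centre prior to each dispensing of lenalidomide". The form's own header says the same: "To be completed prior to each dispensing of lenalidomide".

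**The bar.** Under the grounds for not dispensing, the form lists: "The patient states she/he did not use TWO reliable methods of birth control (unless practicing complete abstinence of heterosexual intercourse"). The bracket that follows gives the period: "at least 28 days prior, during, dose interruption and 28 days after discontinuation of lenalidomide".

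**The rule for men elsewhere.**
- Inclusion criterion 9 (Synopsis and Section 9.1.3): "Males (including those who have had a vasectomy) must use barrier contraception (condom) when engaging in sexual activity with WCBP".
- Section 21.3.1, male patients before starting product: "Must practice complete abstinence or agree to use a condom during sexual contact with women of childbearing potential while participating in the study". The rule then runs through dose interruptions and for 28 days after the product is stopped. The counselling and on-study text of 21.3.1 also speaks of condom use only.
- The male section of the same form: "To engage in complete abstinence or use a condom when engaging in sexual intercourse (including those who have had a vasectomy"), again with a woman of childbearing potential.

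**The two-method rule elsewhere.** In the rest of Section 21.3 it is stated for women of childbearing potential only: the contraception and on-study text of 21.3.1 and that group's section of the form.

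**The concern.** The form is an operative instruction, not background: someone signs it each time lenalidomide is handed out. Its pronouns cover both sexes, so a rule that the rest of the ex-EU plan reserves for women of childbearing potential is extended to men. A site cannot follow both the item and the male rule for a man who relies on a condom alone.

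A site that applies the item literally refuses drug to a subject who meets the eligibility criteria and has been counselled as the form directs. A site that follows the male section signs a form whose list forbids what it has just done. Sites may differ in how they apply a pregnancy-risk control that ought to be unambiguous.

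**Working it through.** No arithmetic applies. The check sets the passages side by side and asks, for each kind of subject, whether the two sets of text agree.

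| Subject (ex-EU plan) | Criterion 9, 21.3.1 and the subject's own section of the form | Do-not-dispense item |
|---|---|---|
| Man, completely abstinent | Satisfied | Exempt, may be dispensed |
| Man, partner of childbearing potential, condom only | Satisfied | Barred |
| Man, partner of childbearing potential, condom plus a partner's method in place over the stated period | Satisfied | Not barred, if the partner's method is counted |
| Man, not abstinent, partner not of childbearing potential, fewer than two methods | No contraceptive method required | Barred |
| Woman not of childbearing potential, not abstinent, fewer than two methods | No contraception duty listed in her section | Barred |
| Woman of childbearing potential, not abstinent, fewer than two methods | Not satisfied | Barred (the texts agree) |

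The texts conflict in rows two, four and five.

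**Timing.** The item's period begins at least 28 days before lenalidomide. The male text of 21.3.1 begins with study participation and the form's male section begins with taking the drug. Neither has a lead-in. At first dispensing, a man told only the condom rule may therefore be unable to meet the item's period, even if he has since added a second method.

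**Can the item be read as limited to women of childbearing potential?** Not from its wording. It names both sexes, and the ground just above it, on missing pregnancy tests, is expressly limited to women of childbearing potential. The list makes that restriction in one line and not in the next.

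**Territory.** The European form in Section 21.4.2 has no do-not-dispense list and counsels men on condoms only, so the conflict does not arise there. The opening sentence of 21.3 speaks of all patients receiving lenalidomide. I read it within the territorial limit of its heading, because the inclusion criteria refer to Section 21.3 or 21.4.

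**The case against.** The best answer is that nobody would be misled. The form has separate sections for women of childbearing potential, women not of childbearing potential, and men, and the male section states the male requirement plainly. That the literal item would also bar women with no contraception duty suggests a loosely worded checklist line, not an intended second rule for men. The item is also the stricter of the two texts, so applying it would not weaken pregnancy prevention.

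Much of this stands, and it is why the point is minor. But the sensible reading works only by disregarding the item's own pronouns, on a form that must be signed before drug is released. The text is wrong as written, not merely thin on detail.

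A reader might infer more than the documents support:
- *That eligible men in general cannot receive lenalidomide.* The item exempts complete abstinence, a couple using two methods may satisfy it, and it is absent from the European form.
- *That refusal leads to permanent discontinuation.* Section 10.3 says: "Any investigational product (lenalidomide and/or cetuximab) held > 14 days must be discontinued". That sentence names no reason for the hold, but it sits among rules on toxicity and dose changes. Nothing says that a contraception-based refusal to dispense counts as a hold, and a refusal at first dispensing interrupts nothing already begun.
- *That dispensing to such a man is a protocol violation under Section 10.6, or that responses would be lost.* Section 10.6 lists protocol violation only as a general reason for stopping treatment. No passage classifies dispensing to a man who meets criterion 9 as one, and nothing in the protocol supports a lost response.

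**Conclusion.** The contradiction is real and limited. On the ex-EU form, the do-not-dispense item applies a two-method rule, with a lead-in of at least 28 days, to anyone not completely abstinent. This conflicts with the condom-only male rule in criterion 9, Section 21.3.1 and the form's own male section. It also reaches non-abstinent women not of childbearing potential. If the form is followed as written, non-abstinent men without a second method who meet criterion 9 cannot be dispensed lenalidomide.

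The number affected cannot be estimated. The protocol gives neither the proportion of men nor the proportion enrolled outside the EU, and the 220 total is a ceiling that includes a conditional Expansion part. Sample size, error rate, endpoint and analysis are unaffected. Severity is minor. The conclusion assumes only that the item is read literally and that Section 21.3 applies outside the EU, as its heading says. Which of the conflicting requirements is right is not for this review to say.

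**What to change.** Reconcile these places: criterion 9 in the Synopsis and Section 9.1.3; the counselling, pre-treatment and on-study text for men in Section 21.3.1; and, in Section 21.3.2, the do-not-dispense list, the section for women not of childbearing potential and the male section. Then replace the single item with one line for each group (women of childbearing potential, women not of childbearing potential, and men). Each line should repeat the requirement and the period that the reconciled text states for that group, or state that none applies.

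The cost is one item on an appendix form, with any matching wording the sponsor decides on, carried in the next amendment. It adds no visits, tests or subjects.
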